#### 3.2.6. Self-Reported Sedentary Behavior

The Spanish version of the Sedentary Behavior Questionnaire (SBQ-S) [73] will be used to assess self-reported sedentary behavior. Participants will report how long they spent in 11 different sedentary behaviors. Response options are none, 15 min or less, 30 min, 1 h, 2 h, 3 h, 4 h, 5 h, or 6 h or more. This questionnaire has demonstrated adequate reliability and validity in adult populations and has also been previously employed in individuals with chronic pain [73].

#### 3.2.7. Quality of Life and Mental Health

The 36-item Short-Form Health Survey (SF-36) [74] will be used to evaluate health-related quality of life. It contains 36 items grouped into 8 dimensions. The scores range from 0 to 100 in every dimension, where higher scores indicate better health. It has demonstrated appropriate validity [74].

The Beck Depression Inventory-II (BDI-II) [75] will be used to assess depression severity. It contains 21 items assessing depressive symptoms, ranging from 0 (not present) to 3 (severe), according to how they have been feeling during the previous two weeks. The range score is 0–63: minimal (0–13); mild (14–19); moderate (20–28); and severe (29–63).

The State-Trait Anxiety Inventory-I (STAI) [76] will be used to evaluate the level of current anxiety. It is a 20-item self-administered questionnaire in which individuals are asked to indicate the score from 0 to 3 that best indicates how they feel at the time they are filling in the questionnaire. The range of scores is 20–80: no anxiety (≤20), mild (21–39), moderate (40–59), and severe anxiety (60–80).

#### 3.2.8. Sleep Quality

The Pittsburgh Sleep Quality Index (PSQI) will be used to assess the sleep duration and quality [77]. The PSQI is 19 items composed of 7 subscales, where scores range from 0 to 3 (global score 0–21). Higher scores indicate poor sleep quality. This instrument has been previously used in studies involving individuals with chronic pain [78].

#### 3.2.9. Central Sensitization

The Central Sensitization Inventory (CSI) will be used to evaluate symptoms related to central sensitization (CS) and central sensitivity syndromes (CSS) [79,80]. It contains 25 statements related to current health symptoms. Each of these items is measured on a 5-point temporal Likert scale. The score range is 0–100: subclinical (0 to 29), mild (30 to 39), moderate (40 to 49), severe (50 to 59), and extreme (60 to 100). CSI has demonstrated good reliability, internal consistency, and construct validity [80].

#### 3.2.10. Rate of Perceived Exertion

RPE based on the Borg CR-10 scale will be used to assess training intensity. It is a 10-point scale ranging from 0 (“nothing at all”) to 10 (“very, very strong”) [81]. It represents a valid and moderately reliable tool for monitoring exercise intensity in chronic pain populations [82]. At the end of each session, the participants will determine the subjective intensity of the session. The CR-10 will also be used after performing each physical fitness test during assessments.

## 4. Statistical Analysis

Since this study aims to determine the potential efficacy and effectiveness of supervised exercise programs and mindfulness, statistical analysis will be performed using both per-protocol and intention-to-treat approaches (with ≥70% attendance required for inclusion). The effects of the intervention will be assessed as between-groups differences in changes from baseline to post-intervention in primary and secondary outcomes using one-way analysis of covariance (ANCOVA). The mean change (post-intervention minus baseline values) will be used as the dependent variable, the group as the fixed factor, and the baseline value of the outcome as a covariate. The same approach will be applied to evaluate the persistence of changes at follow-up. Given the repeated-measures design, linear mixed models will also be used to examine group-by-time interactions across all time points. This approach accommodates missing data under the missing-at-random assumption and accounts for within-subject correlation, providing a more robust framework than ANCOVA for longitudinal analyses. All analyses will be adjusted for potential confounding variables that are not well balanced at baseline. Sex will be used as a potential covariate in all analyses to explore whether the intervention effects differ between men and women, and whenever possible, the sample will be stratified by sex. Cohen’s d will be calculated to determine standardized effect sizes. To control for type I error due to multiple comparisons, the Bonferroni correction will be applied when conducting post hoc analyses or when evaluating multiple outcome variables. Statistical significance will be set at α = 0.05. All analyses will be performed using the Statistical Package for the Social Sciences (SPSS) for Windows, Version 27.0. (IBM Corp., Armonk, NY, USA).

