## Abstract

**Introduction:** Chronic primary low back pain (CPLBP) is a prevalent condition in primary care and a leading cause of disability and absenteeism worldwide. Multidimensional approaches may be necessary to achieve physical and mental health benefits in individuals with CPLBP. **Objective:** The BACKFIT randomized controlled trial aims to evaluate the effectiveness of a multidimensional intervention—combining supervised exercise and mindfulness—on pain, physical fitness, mental health, and functional outcomes in individuals with CPLBP. **Hypothesis:** Both the supervised exercise program focused on motor control and trunk muscle strength (IG1) and the multidimensional intervention combining supervised exercise with mindfulness training (IG2) are expected to produce significant health improvements in individuals with CPLBP. It is further hypothesized that IG2 will yield greater improvements compared to IG1, both immediately post-intervention and at the two-month follow-up. **Design:** Randomized controlled trial. **Setting:** Virgen de las Nieves University Hospital, Granada (Spain). **Participants:** 105 individuals. Inclusion criteria: Previously diagnosed with CPLBP, aged ≥18 and ≤65 years, able to read and understand the informed consent, and able to walk, move, and communicate without external assistance. Exclusion criteria: serious lumbar structural disorders, acute or terminal illness, physical injury, mental illness, and medical prescriptions that prevent participation in the study. **Intervention:** Individuals will be randomly assigned to a supervised physical exercise group (2 days per week, 45 min per session), a multidimensional intervention group (same as supervised physical exercise group, and mindfulness 1 day per week, 2.5 h per session) or an active control group (usual care, 2 days per week, 45 min per session). The intervention will last 8 weeks. **Main Outcome Measures:** Primary outcome: pain threshold, perceived acute pain, and disability due to pain. Secondary measures: body composition, muscular fitness, gait parameters, device-measured physical activity and sedentary behavior, self-reported sedentary behavior, quality of life, pain catastrophizing, mental health, sleep duration and quality, and central sensitization. The groups will undergo pre-intervention, post-intervention, and a 2-month follow-up after a detraining period. **Statistical Analysis:** Both per-protocol and intention-to-treat approaches (≥70% attendance) will be used. Program effects will be assessed via one-way ANCOVA for between-group changes in primary and secondary outcomes. **Conclusions:** Given the complex nature of CPLBP, multidimensional approaches are recommended. If effective, this intervention may provide low-cost alternatives for health professionals.

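### Two analyses, a per-visit ANCOVA and a mixed model, are planned for the same outcomes and neither is named as the one that decides

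*Protocol article*

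**What the plan says.** The first analysis in Section 4 (Statistical Analysis) concerns between-group differences in "changes from baseline to post-intervention in primary and secondary outcomes using one-way analysis of covariance (ANCOVA"). Its form is fixed: "The mean change (post-intervention minus baseline values) will be used as the dependent variable, the group as the fixed factor", with the baseline value as covariate. For the two-month visit, "The same approach will be applied to evaluate the persistence of changes at follow-up".

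The section then states that "linear mixed models will also be used to examine group-by-time interactions across all time points". Of this second method it says "This approach accommodates missing data under the missing-at-random assumption and accounts for within-subject correlation", and it ranks the method above the first as "providing a more robust framework than ANCOVA for longitudinal analyses".

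The abstract mentions one method only: "Program effects will be assessed via one-way ANCOVA for between-group changes in primary and secondary outcomes". Section 2.2 (Participants) plans for roughly 20–30% dropout. No sentence names a primary analysis or says what happens if the two disagree. The Bonferroni rule covers post hoc comparisons and multiple outcomes, not two models applied to one outcome.

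**The concern.** The article commits to two methods that can each give an effect for the same outcome at the same visit. Its own signals about which one counts conflict. Order of presentation and the abstract point to ANCOVA; the stated ranking for longitudinal data with missing values points to the mixed model.

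Two things are at stake. First, if the results differ, either can be presented as the finding, and choosing after the data are seen raises the false-positive rate. Second, the methods treat dropout differently. A change score needs both visits, so without imputation ANCOVA at follow-up makes no use of the post-intervention score of someone who leaves before follow-up. A likelihood-based mixed model does use it. If poor responders leave one arm more often, the claim of persistence at two months is affected.

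**Working it through.** **Inputs from the protocol article.** Three arms of 35, total 105; 26 per group before dropout; power 0.80, alpha 0.05, effect size 0.70; dropout 20–30% (Section 2.2). Visits are t0, t1 (post-intervention) and t2 (two months).

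**Assumed, not in the document.** Correlation ρ between visits of 0.5 to 0.7, equal for all pairs; normal outcomes in SD units; dropout missing at random given earlier scores.

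**Step 1: the plan's own figure.** n per arm = 2(z_α + z_β)²/d². With one-sided α = 0.05 this is 2(1.645 + 0.842)²/0.49 = 25.2, so 26. Allowing for 25% dropout, 26/0.75 = 34.7, so 35 per arm and 105 in total. The stated figures reproduce on that basis. With two-sided α the formula gives 2(1.960 + 0.842)²/0.49 = 32.0, rounded up to 33 (34 by noncentral t). Sidedness is a separate matter and is not used below.

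**Step 2: is ANCOVA the less powerful test?** The variance of the baseline-adjusted contrast relative to the plain change-score contrast is (1 − ρ²)/[2(1 − ρ)] = (1 + ρ)/2, which is 0.75 at ρ = 0.5 and 0.85 at ρ = 0.7. With complete data, a mixed model that leaves baseline means free by arm gives the change-score contrast, so ANCOVA is the more precise of the two. At 26 per arm and ρ = 0.5 the ANCOVA standard error is √(2 × 0.75/26) = 0.240 SD, and power for 0.70 SD is 0.82 (two-sided 0.05).

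Power for one pairwise contrast was also simulated with 35 per arm, 25% dropout by t2, a true effect of 0.70 SD and 1,500 runs per scenario:

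| Visit, ρ | ANCOVA | Mixed model, free baseline | Mixed model, common baseline |
|---|---|---|---|
| t1, 0.5 | 0.873 | 0.781 | 0.880 |
| t1, 0.7 | 0.956 | 0.928 | 0.958 |
| t2, 0.5 | 0.810 | 0.747 | 0.836 |
| t2, 0.7 | 0.931 | 0.915 | 0.950 |

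**Step 3: the open choice.** In the same simulation with no true effect, ANCOVA and the free-baseline mixed model each reject in 0.047–0.059 of runs. Reporting whichever is significant rejects in 0.072 (t1) and 0.073 (t2) at ρ = 0.5, and in 0.079 and 0.065 at ρ = 0.7. The Monte Carlo standard error is √(0.05 × 0.95/1500) ≈ 0.006. With a true effect of 0.70 SD, the two tests disagree on significance in about 13% of trials at ρ = 0.5 and 4–5% at ρ = 0.7. If the mixed model instead has a common baseline mean, the either-test error is only 0.055–0.061.

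**Step 4: dropout and bias.** Given baseline, the covariance of the t1 and t2 scores under equal correlation is ρ − ρ²: 0.25 at ρ = 0.5 and 0.21 at ρ = 0.7. Adjusting for baseline alone therefore does not remove selection that acts through the t1 score. Assume no true effect and dropout before t2, driven by the t1 score, of 30% in one arm and 15% in another. ANCOVA at t2 is then biased by about 0.03 SD (up to about 0.05 in one set-up) towards the arm that loses more people; the likelihood estimate is off by 0.005 SD or less. In the power simulation, with a true effect of 0.70, both methods estimate 0.69–0.70 at t1. At t2 ANCOVA gives 0.67 and the mixed models 0.69–0.70.

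A bias of 0.03 SD is 0.03/0.70 ≈ 4% of the planning effect. It is about 0.13–0.15 of a standard error, taking 0.240 at ρ = 0.5 and √(2 × 0.51/26) = 0.198 at ρ = 0.7.

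**The case against.** The strongest reply is that the two methods have different jobs: ANCOVA for the effect at a visit, the mixed model for the pattern across visits. The claim of greater robustness is limited to longitudinal data, and an abstract must be short. A statistical analysis plan, not shown here, may name the primary analysis.

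Part of this stands. Covariance structure, contrast coding and the handling of missing data in ANCOVA are normally left to a fuller document, and their absence is no finding. But the article does more than leave a gap. It commits to both methods for the same outcomes and applies ANCOVA again at follow-up, which is where its own reason for preferring the mixed model applies. A later plan would have to overrule one of these signals.

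A reader might also infer three stronger points, which the document does not support:

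- *The weaker test leads.* In power it does not (Step 2). The mixed model is better only in the article's own sense of coping with missing longitudinal data. That ANCOVA leads at all is read from its position and the abstract; it is never labelled primary.
- *The mixed model is only an omnibus test.* Three arms and three visits would give an overall interaction test with (3 − 1)(3 − 1) = 4 degrees of freedom, which would not answer IG2 versus IG1 at a given visit. But the text speaks of interactions in the plural and provides for post hoc comparisons, so a single overall test is an inference.
- *ANCOVA uses available pairs.* This follows from the change score if nothing is imputed, but it is not stated.

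The bias argument is also modest: small, confined to follow-up, and dependent in direction on the dropout pattern assumed.

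**Conclusion.** The point holds in limited form. Two analyses of the same outcomes are planned, none is named as decisive, and the article's stated preference conflicts with its order of use and its abstract.

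The size is moderate. Type I error per contrast and visit is about 0.065–0.08 if the choice is made after seeing results. That figure assumes visit correlations of 0.5–0.7 and free baseline means, and it nearly disappears if the mixed model shares a baseline mean across arms. The follow-up bias of ANCOVA, about 0.03 SD under an assumed 30% versus 15% dropout driven by the post-intervention score, is a secondary reason. The comparison at post-intervention is not at risk from low ANCOVA power, and under the dropout simulated both methods are close to unbiased there.

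**What to change.** Name one primary analysis in Section 4: a linear mixed model on all randomised participants, using t0, t1 and t2, with unstructured covariance, a common baseline mean across arms, and adjustment for the stratification factors age and sex. Estimate the pairwise group contrasts from it, at t1 as primary and t2 as secondary. Keep ANCOVA on change as a sensitivity analysis, and do not use the overall group-by-time p-value as a decision test. Revise the abstract to match.

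The attendance condition attached to the analysis approaches, "statistical analysis will be performed using both per-protocol and intention-to-treat approaches (with ≥70% attendance required for inclusion"), must not limit who enters this model. Randomisation follows the baseline evaluations (Section 2.3), so each randomised participant should have a t0 value to contribute.

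This keeps ANCOVA's power at post-intervention (0.880 versus 0.873 at ρ = 0.5; 0.958 versus 0.956 at ρ = 0.7) and gains about 0.02–0.03 at follow-up. The cost is changed wording and slightly more modelling work in SPSS, mainly coding the common baseline mean. No additional data are needed, and both types of analysis are already planned.

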### 2.2. Participants

This RCT, based on a supervised exercise program and mindfulness intervention, was prescribed and planned by physical therapists and sports science professionals, and it will be conducted in Granada (southeastern Spain). Based on previous literature [22], with a statistical power of 0.80, an alpha error of 0.05, and an effect size of 0.70, a sample size of 26 participants per group is sufficient to find differences in pain after the intervention. Considering a dropout rate of approximately 20–30%, as reported in similar studies involving pain populations [39], the total sample size will be set at 105 participants, randomly assigned to intervention group 1 (IG1, *n* = 35), intervention group 2 (IG2, *n* = 35) and control group (CG, *n* = 35). The inclusion and exclusion criteria are described in Table 2.

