Once the baseline evaluations have been completed, participants will be randomized into different groups to reduce the risk of bias during the assessment. A computer-generated randomization sequence stratified by two factors (age at study entry and sex) will allocate participants to each group. This randomization sequence will be created by a blinded researcher external to the project using computer software. The allocation will be concealed in a password-protected computer file.

The groups will undergo pre-test (before the intervention), post-test (after each intervention), and follow-up (after an 8-week detraining period) measurements.

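### Covariates enter by observed baseline imbalance, while age, a stratification factor, is not named in the model and sex is only a potential covariate

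*Protocol article*

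**What the plan says.** On allocation, the protocol article, section 2.3 (Recruitment and Randomization), states: "A computer-generated randomization sequence stratified by two factors (age at study entry and sex) will allocate participants to each group". Baseline evaluations are completed before participants are randomised.

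On the model, section 4 (Statistical Analysis) takes the change from baseline as the dependent variable, with "the group as the fixed factor, and the baseline value of the outcome as a covariate". The same approach is used at follow-up, and linear mixed models are added across all time points.

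On further covariates, section 4 adds: "All analyses will be adjusted for potential confounding variables that are not well balanced at baseline". It names no candidate variables and gives no threshold or timing for judging imbalance.

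On sex, it says: "Sex will be used as a potential covariate in all analyses to explore whether the intervention effects differ between men and women". Separate analysis of each sex is foreseen only conditionally: "whenever possible, the sample will be stratified by sex". Age is not mentioned in section 4.

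**The concern.** The analysis does not follow the design. Two variables were thought important enough to stratify on. One is absent from the model, and the inclusion of the other is left open by the word potential.

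The rule that fills the gap selects on the wrong criterion. In a properly randomised trial, a baseline difference between arms is a chance event. It says nothing about whether the variable predicts outcome, and prediction of outcome is what makes adjustment worthwhile. The rule also works against the stratification: because allocation tends to balance age, age will tend not to qualify.

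Two things are at stake. One is precision: a prognostic stratification factor left out of the model stays in the error term, so intervals are wider than the design warrants. The other is a settled primary model: without a list or threshold, two analysts could apply the sentence to the same baseline table and fit different models.

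The sentence on sex has its own difficulty. A main-effect covariate adjusts for sex but cannot show whether effects differ between men and women. That takes a group-by-sex interaction.

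**Working it through.** **1. Design against analysis**

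| Variable | Used in allocation (section 2.3) | Place in the analysis (section 4) |
|---|---|---|
| Baseline value of outcome | no | fixed covariate |
| Age at entry | stratification factor | not named; could enter only through the imbalance rule |
| Sex | stratification factor | potential covariate, for exploring effect differences |
| Any other variable | no | enters if judged not well balanced |

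**2. Size of the precision loss**

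The documents give no correlation of age or sex with any primary outcome. Let R² be the share of residual variance, after the baseline value, that the omitted factors explain. Assumed range: 5–15%.

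- Ratio of interval widths, adjusted to unadjusted: √(1 − R²). √0.95 = 0.975 and √0.85 = 0.922, so intervals narrow by about 2.5% to 8%.
- Equivalent gain in information: 1/(1 − R²) − 1. 1/0.95 − 1 = 5.3% and 1/0.85 − 1 = 17.6%, so about 5% to 18%.
- At R² near 0, both gains are near 0.

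**3. Effect on the test**

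When a factor is balanced by design, the treatment estimate varies only with the remaining error, but the model without the factor reports a standard error larger by 1/√(1 − R²). The large-sample two-sided error rate is then 2Φ(−1.96/√(1 − R²)).

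- R² = 5%: 1.96/0.975 = 2.01, giving 4.4%.
- R² = 15%: 1.96/0.922 = 2.13, giving 3.4%.

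Both are below the nominal 5%, so the test is conservative.

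**4. Simulation as a check**

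Setting: two arms of 26, age and sex balanced by stratification, two-sided alpha 0.05, standardised difference 0.70. The 26 and the 0.70 come from section 2.2 ("a sample size of 26 participants per group is sufficient to find differences in pain after the intervention", "with a statistical power of 0.80, an alpha error of 0.05, and an effect size of 0.70"). Assumption: age and sex each correlate with outcome at r, so for independent factors joint R² = 2r². The baseline outcome was not modelled, and both factors were left out together. There were 4,000 runs for type I error and 2,000 for power.

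| r for each factor | Joint R² | Type I error, omitted | Type I error, included | Power, omitted | Power, included |
|---|---|---|---|---|---|
| 0.20 | 8% | 4.3% | 5.3% | 70% | 72% |
| 0.30 | 18% | 3.0% | 5.0% | 71% | 79% |
| 0.35 | 24.5% | 2.3% | 5.0% | 72% | 81% |

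The type I error agrees with the formula in step 3, which gives 4.1%, 3.0% and 2.4%. The last two rows lie above the 5–15% range and should be read as upper cases.

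**5. The plan's own figure**

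This point disputes no stated number. The 26 per group reproduces with a one-sided alpha of 0.05 (two-sided needs 33 to 34; the article does not state sidedness), and 26/0.75 rounds up to the 35 per arm planned. That question is separate, and nothing here depends on it.

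**The case against.** **Sex is named.** A reader might infer that both stratification factors are ignored. The text does not support that: sex is named for all analyses, and analysis by sex is foreseen where possible. What stands is that the word potential leaves its inclusion open and that the stated purpose is effect modification, not adjustment. The clear omission is age.

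**No bias.** A reader might infer that leaving age out distorts the treatment effect. It does not. Age is balanced by allocation, and the cost is in precision.

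**Baseline may already do the work.** The model conditions on the outcome's baseline value, which may absorb much of any age effect. This stands. The relevant R² is what age adds beyond baseline, and sex if it is included, and it could be close to zero.

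**The rule need not be post hoc.** A reader might infer that covariates will be picked with results in view, or by significance tests on many baseline variables. Neither is stated. Baseline data are complete before randomisation, so imbalance can be judged before any outcome is seen, and the restriction to potential confounders implies some judgement of relevance. What stands is that the selection criterion is wrong and that list, threshold and timing are open.

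**An article condenses.** A covariate list may well sit in an analysis plan that is not shown, and its absence alone would be no finding. But the article states a selection rule for all analyses. A plan that followed the rule would carry the problem forward; one that did not would contradict the article.

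**Conclusion.** The point holds as one of efficiency and prespecification. The article stratifies on age and sex, fixes neither firmly in the model, and chooses other covariates by a criterion that does not identify prognostic variables and tends to pass over age.

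If the omitted factors explain 5–15% of residual variance, intervals are wider than they need be, and including the factors would narrow them by about 2.5–8%, worth about 5–18% more information. The range is an assumption, since the documents supply no correlations. If sex is in fact included, the loss comes from age alone and may be smaller; if age adds little beyond the baseline value, it may be negligible. Any error is in the conservative direction. The change is worth making because it is almost free, whatever the size of the gain.

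**What to change.** Replace the imbalance sentence and the sentence on sex in section 4 with wording to this effect:

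- All ANCOVA and mixed models include group, the baseline value of the outcome, age at entry and sex as prespecified covariates. The form in which age enters is stated.
- No covariate is added to the primary analysis because of observed baseline imbalance. Any such adjustment is a labelled sensitivity analysis.
- Differences in effect between men and women are examined with a group-by-sex interaction in a separate analysis labelled exploratory.

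The cost is a wording change and a few degrees of freedom. Age and sex are already recorded because allocation requires them, and the planned sample size does not change.

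### Using sex as a covariate cannot show whether intervention effects differ between men and women; the sex-stratified analyses planned alongside have no stated comparison between them.

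*Protocol article*

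**What the plan says.** Section 4 (Statistical Analysis) specifies an ANCOVA on the change score, with "the group as the fixed factor, and the baseline value of the outcome as a covariate". It adds that "linear mixed models will also be used to examine group-by-time interactions across all time points". Group-by-time is the only interaction named in the article.

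On sex, the section gives two instructions in one sentence. The first is a covariate with a declared purpose: "Sex will be used as a potential covariate in all analyses to explore whether the intervention effects differ between men and women". The second is conditional: "whenever possible, the sample will be stratified by sex". It does not say how results in men and women would be compared.

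Sex also enters the design. Section 2.3 states: "A computer-generated randomization sequence stratified by two factors (age at study entry and sex) will allocate participants to each group".

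**The concern.** The sentence ties a method to a purpose that the method cannot serve. A sex covariate estimates the average difference in outcome between men and women and holds the group effect equal in both. Whether the group effect differs by sex is a question about a group-by-sex term, and none is named.

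The stratified analyses come closer, because they estimate the effect separately in each sex. Without a stated comparison, though, a reader of the results is left with two sets of p-values from small subgroups. If one is significant and the other is not, it is easy to report that the intervention works in one sex only, even when the true effects are the same. What is at stake is a secondary, exploratory statement about sex, not the main comparison of the arms.

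**Working it through.** **Inputs from the documents.** Section 2.2 plans "with a statistical power of 0.80, an alpha error of 0.05, and an effect size of 0.70" and concludes that "a sample size of 26 participants per group is sufficient to find differences in pain after the intervention". Enrolment is 35 per arm, 105 in total. Section 4 sets α = 0.05, with Bonferroni correction for post hoc analyses or multiple outcomes.

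**Assumptions.** The sex ratio is not given, so 50–80% women is used. Evaluable numbers run from 26 (the planned minimum) to 35 (no dropout) per arm. Tests are two-sided and concern one pairwise contrast. Effects are in units of the SD of the analysed outcome.

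**The plan's own figures.** With n = 2(z_α + z_β)²/d²:
- One-sided: 2(1.645 + 0.842)²/0.70² = 25.2, so 26 per group. This reproduces the plan.
- Two-sided: 2(1.960 + 0.842)²/0.70² = 32.0, so 33 per group.
- Dropout at 25%: 26/0.75 = 34.7, so 35 per arm, and 3 × 35 = 105. This reproduces the plan.

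The sidedness does not affect the present point. The figures serve only to fix the subgroup sizes.

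**Step 1. What a sex covariate detects.** 4,000 trials were simulated with 26 per arm and a 50:50 sex split:

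| Truth | Sex covariate significant | Group-by-sex term significant |
|---|---|---|
| Average sex difference 0.70 SD, same group effect in both sexes | 69% | 5% |
| Group effect 0 in one sex and 1.4 SD in the other, no average sex difference | 4% | 70% |

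The covariate responds when effects do not differ and stays silent when they do.

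**Step 2. Sex-split tests when the true effect is identical (0.70 SD).** Let p_W and p_M be the t-test power in women and in men. The two tests use different patients, so the chance that exactly one is significant is p_W(1 − p_M) + p_M(1 − p_W).

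Example: 26 per arm at 50:50 gives 13 per arm per sex and power 0.403 in each. Then 2 × 0.403 × 0.597 = 0.481.

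| Per arm | Women | Power in women / men | Exactly one significant, α = 0.05 | α = 0.05/3 | α = 0.05/9 |
|---|---|---|---|---|---|
| 26 | 50% | 40% / 40% | 48% | 36% | 23% |
| 26 | 70% | 54% / 25% | 52% | 39% | 25% |
| 26 | 80% | 60% / 17% | 56% | 43% | 28% |
| 35 | 50% | 52% / 52% | 50% | 45% | 33% |
| 35 | 70% | 67% / 33% | 56% | 50% | 37% |
| 35 | 80% | 73% / 23% | 63% | 55% | 41% |

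The power column is at α = 0.05. The divisors 3 (three pairwise contrasts) and 9 (three contrasts by three primary outcomes) are assumptions, because the article does not say how many comparisons the Bonferroni correction would count.

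**Step 3. What a group-by-sex term would deliver.** For one contrast, SE = √(2/n_W + 2/n_M), where n_W and n_M are the women and men per arm. Power for a between-sex difference of 0.70 SD is about Φ(0.70/SE − 1.96).
- 26 per arm, 50:50: SE = √(4/13) = 0.555, and Φ(1.262 − 1.96) = 0.24.
- 26 per arm, 80% women: SE = √(2/20.8 + 2/5.2) = 0.693, and power is 0.17.
- 35 per arm: power is 0.31 at 50:50 and 0.22 at 80% women.

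The difference detectable with 80% power is 2.80 × SE. That is 1.55–1.94 SD at 26 per arm and 1.34–1.67 SD at 35 per arm. Detecting 0.70 SD with 80% power at 50:50 would take 8 × (2.8016/0.70)² = 128.1, so 129 evaluable per arm.

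**The case against.** The strongest reply has four parts.

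- **The plan does more than add a covariate.** Sex-stratified analyses appear in the same sentence, and their estimates do bear on whether effects differ. This stands. A reader might infer that sex enters only as a covariate, or that the plan as a whole cannot address the question. The text does not support either reading.
- **No p-value contrast is written down.** A reader might infer that the plan will compare significance in men with significance in women, and so that the stratified analyses would mislead. The article states no such rule, and it plans Cohen's d, which is an effect-size measure. This also stands. The discordance figures show what would happen if significance were contrasted; they do not describe a stated procedure.
- **Bonferroni lowers the figures.** It does, and the ranges above include it.
- **The question is exploratory, and model terms can wait for a statistical analysis plan.** The aim, hypotheses and expected results contain no sex hypothesis, so the low weight is right. The deferral argument does not remove the point. The article does not leave the method open: it names covariate use as the means of exploring differing effects, and it names an interaction elsewhere where it wants one.

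One could add that the interaction test would itself miss a 0.70 SD difference about 69–83% of the time. That is true, but an estimate with its confidence interval displays this uncertainty, whereas two separate p-values conceal it.

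**Conclusion.** The point holds as a mismatch between method and purpose. Covariate adjustment for sex cannot show differing intervention effects, whatever the sample size or sex ratio. The stratified analyses are valid within each sex but lack a stated comparison.

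If significance were contrasted between the sexes while the true effect is 0.70 SD in both, a discordant result would arise in about 48–63% of trials at two-sided 0.05, or about 23–55% with alpha divided by 3 to 9. These figures rest on the assumed 50–80% women, 26–35 evaluable per arm and the assumed divisors.

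The sentence should be changed, but the consequence is limited to exploratory statements about sex. No primary conclusion depends on it.

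**What to change.** Replace the sentence on sex in section 4 with text to this effect: sex and age at entry are included as adjustment covariates in all models because randomisation is stratified by both. Whether effects differ by sex is explored with a prespecified group-by-sex term in the ANCOVA and a group-by-sex-by-time term in the mixed model, reported as estimates with 95% confidence intervals. Sex-specific effects are taken from those models, and significance in one sex is not contrasted with significance in the other.

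The article does not say whether the ANCOVA or the mixed model is primary, so the term should be specified for both.

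The cost is a few lines of text and one additional exploratory term per model, with no extra data or participants. The drawback is imprecision: power is about 17–31% for a 0.70 SD difference at two-sided 0.05. The analysis must therefore be labelled exploratory, and a non-significant interaction must not be read as evidence that effects are equal.
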